## Abstract

**Introduction:**

Shoulder pain is a common reason for physiotherapy consultations, and the high prevalence of rotator cuff-related shoulder pain (RCRSP) calls for novel approaches. Immersive virtual reality (IVR) offers an innovative treatment option to reduce pain, improve mobility and function in RCRSP. This study aims to compare the effectiveness of combining IVR with standard treatment versus standard treatment alone on clinical variables, clinimetric measures, and biomarkers in individuals with chronic RCRSP.

**Materials and methods:**

A single-blind, multicentre randomized clinical trial will be conducted. Participants will be randomly assigned to two groups: the control group will undergo a three-month exercise program, while the intervention group will receive an IVR program for the first month, followed by the same exercise program for the control group during second and third months. Clinical, clinimetric, and biomarker variables will be assessed at baseline and at follow-ups at 1, 2, and 3 months.

**Results:**

This study will shed light on the effectiveness of the combined program of immersive virtual reality with exercise and exercise program alone in chronic RCRSP patients. Measurements of clinical, clinimetric, and biomarker variables will help to explore how these interventions may influence this clinical population within a comprehensive perspective.

**Conclusions:**

This study protocol outlines a novel approach to managing chronic rotator cuff-related shoulder pain by integrating IVR with exercise-based physiotherapy. The results will provide valuable insights into the additive effects of IVR on variables such as pain, function, psychosocial factors and biological markers, potentially informing future rehabilitation strategies and enhancing patient outcomes in musculoskeletal care.

## Introduction

Shoulder pain is one of the main reasons for consultation in physiotherapy [1], and rotator cuff-related shoulder pain (RCRSP) reflects 50%–85% of diagnoses for shoulder pain [2]. The high prevalence of RCRSP [3] requires research on new treatment approaches that can improve clinical results of usual physiotherapy care. That is why the treatment modality that is most effective in RCRSP is still under debate with conflicting findings and large heterogeneity [4]. Within the options available, exercise-based physiotherapy as first-line conservative treatment has been strongly recommended to reduce pain and improve mobility and function in RCRSP [5–7]. However, uncertainties exist regarding the mechanisms of action [8,9], modalities [10–12] and dosage [13,14] of exercise in RCRSP pose a challenge for clinical management. Nevertheless, poor adherence to therapeutic exercise programs has been identified as a major barrier in the management of RCRSP [15]. Enjoying exercise has been shown to be a significant facilitator in adherence to exercise in RCRSP [16].

To overcome such barriers and enhance clinical outcomes, the use of immersive virtual reality (IVR) has been proposed as a novel strategy for the management of patients with chronic pain, disability and loss of quality of life [17]. IVR has shown significant positive effects on pain relief, disability, range of motion (ROM), fear of movement, negative affect, fatigue and anxiety in people suffering from chronic pain [18–21]. Nonetheless, available evidence of IVR in RCRSP is scarce, yet preliminary studies have highlighted the potential of this intervention for reducing pain, increasing ROM [22] and enhancing engagement in exercise rehabilitation programs for shoulder pain [23]. Indeed, individuals with shoulder pain that followed a 3-week programme of gamified IVR-based exercise, added to a home exercise programme, increased shoulder ROM and reduced pain scores [24].

Additionally, IVR is seen as a novel tool to provide motivation and improve patient adherence to rehabilitation protocols, which is crucial for the necessary implementation of long-term treatment and the achievement of positive results [25]. It has been remarked that IVR technology is rapidly evolving, which has an impact on the quality of the user experience, but also on safety and feasibility, for shoulder rehabilitation [26]. Brady et al. (2023) reported that physiotherapists considered that IVR provides new venues for shoulder rehabilitation and may offer new opportunities for the management of fear of movement, as it can provide an engaging platform to enhance motivation to exercise [23]. Likewise, this therapeutic strategy can be adapted according to the individual patient’s needs, understood as their levels of functionality, social context or age, since these can influence adaptability to technology and, therefore, adherence to treatment and the results of IVR [27].

Recently, IVR has proven to be a high-quality treatment option with reduced costs in chronic low back pain [28], which highlights its potential to provide an accessible and effective alternative, reducing the economic burden for both health systems and the patients themselves. These insights suggest that IVR-based exercise therapy can offer an innovative approach to manage patients with RCRSP, improving subjects’ pain experience, functionality and quality of life [29].

The multifaceted nature of RCRSP necessitates a multidimensional assessment approach integrating clinical, clinimetric, and biomarker measures to capture its complex pathophysiology. Clinically, objective measures including pain intensity, ROM, and strength remain fundamental for evaluating functional impairment, though their limitations in correlating with structural pathology underscore the need for complementary outcomes [30]. Psychosocial factors, assessed through clinimetric tools and questionnaires, are critical determinants of chronicity, with low self-efficacy independently predicting persistent pain and disability [31,32]. In this regard, biomarkers might reveal patophysiological insights in shoulder pain. For instance, it has been noted that some inflammatory mediators in the subacromial bursa, including C-reactive protein (CRP), correlate directly with pain intensity or tendon degeneration [33,34], independently of psychosocial factors [35]. Similarly, calcitonin gene-related peptide (CGRP) has been shown to potentially contribute to peripheral sensitization and neurogenic inflammation in chronic pain [33,36], being a neuromodulator in pain processing [37]. Collectively, the integration of clinical, psychosocial, and biomarker domains offers a comprehensive framework for elucidating the biopsychosocial mechanisms underlying RCRSP and for evaluating the efficacy of therapeutic interventions beyond symptomatic relief alone.

To date, no study has compared the effectiveness of the combination of IVR with standard treatment versus standard treatment alone on clinical, clinimetric and biomarker variables in subjects with chronic rotator cuff-related shoulder pain. For this reason, an international multicentre randomized clinical trial could provide a solid starting point for the improvement of rehabilitation strategies and the implementation of new technologies in pain management. Therefore, the purpose of this study is to compare the effectiveness of combining IVR with standard care versus standard care alone on clinical, clinimetric and biomarker variables in individuals with chronic rotator cuff–related shoulder pain. Main outcome was pain intensity, and secondary outcomes included shoulder external rotation isometric strength, hand grip strength, active shoulder range of motion, C-reactive protein (CRP), Calcitonin Gene-Related Peptide (CGRP), shoulder disability, quality of life, fear of movement, pain-related avoidance behaviours, pain hypervigilance, pain self-efficacy, pain-related motor and functional deficits, implicit motor imagery performance and sleep quality.

## Materials and methods

### Study setting

The proposed study is a single blind randomized controlled clinical trial (RCT) with two parallel groups (allocation ratio 1:1). This protocol adheres to the CONSORT (Consolidated Standards of Reporting Trials) guidelines for the publication of clinical trials and will follow the TIDieR (Template for Intervention Description and Replication) checklist, the CERT (Consensus on Exercise Reporting Template) checklist and the SPIRIT (Standard Protocol Item: Recommendations for Interventional Trials) checklist to ensure comprehensive reporting of the interventions. The SPIRIT schedule of enrollment, interventions, and assessments are included in Fig 1. The study has been pre-registered at ClinicalTrials.gov under the identifier NCT06795464 and has been approved by the Ethical Research Committee of the Universidad Francisco de Vitoria with the code 10/2025, and by the Ethical Research Committee of the Universidad Finis Terrae with the code 25–028.

**Fig 1 pone.0341215.g001:**
[figure not shown]
SPIRIT 2025 diagram of the schedule of enrolment, interventions, and assessments.

### Eligibility criteria

Participants will be recruited from two academic institutions: Universidad Francisco de Vitoria (Madrid, Spain) and Universidad Finis Terrae (Santiago de Chile, Chile). These sites were selected based on their accessibility to the target population and their capacity to support clinical research activities. Recruitment will be conducted through institutional mailing lists and printed posters placed in commonly frequented areas within the university campuses.

All recruitment materials will include a brief description of the study, inclusion and exclusion criteria, and contact information for the research team. Interested individuals will be invited to contact the investigators directly to receive detailed information and undergo eligibility screening.

### Participants

Patients with a clinical diagnosis of rotator cuff-related shoulder pain, according to the criteria established by experts for the diagnosis of this entity [38], will be included in the study.

#### Inclusion criteria.

(1) Participants between 18 and 70 years old. (2) Shoulder pain of at least three months of duration, with a pain intensity ≥3 on the Numeric Pain Rating Scale (NPRS). (3) Presence of pain during shoulder movement. (3) Clinical diagnosis rotator cuff-related shoulder pain.

#### Exclusion criteria.

The inclusion criteria include the following: shoulder pain related to the cervical spine, according to the criteria established by experts for the diagnosis of this entity [39]. Presence of pain in the elbow and/or wrist and hand. Clinical diagnosis of frozen shoulder. Clinical diagnosis of shoulder instability. Cognitive deficits. Physiotherapy treatments concomitant to the realization of the study. Traumatic history at the onset of shoulder pain. Previous fractures in the affected shoulder. Previous surgeries in the affected shoulder. Use of analgesic or anti-inflammatory medications within 24 hours prior to participation in the study and at any time during the study. Diagnosis of rheumatic or neurological diseases. Photosensitive epilepsy, severe dizziness, or uncontrolled vestibular disorders, which may prevent or pose a risk during participation in the intervention. Pregnancy or breastfeeding.

All participants who fulfil the eligibility criteria and consent to take part in the study will be required to sign a written informed consent form.

Subsequently, sociodemographic information and baseline clinical, clinimetric and biomarker variables will be gathered. Data collection will take place in a designated room within the universities’ physiotherapy laboratories.

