## Results

According to the recommendations of the Initiative on Methods, Measurement, and Pain Assessment in Clinical Trials (IMMPACT), this study will incorporate multiple measures to evaluate changes in pain intensity, health-related quality of life and functioning, as well as global ratings of improvement [41]. Similarly, the assessment of domains will follow expert consensus from the OMERACT Shoulder Working Group, aligned with the Core Domain Set for Shoulder Disorders [42].

Clinical and clinimetric outcomes will be assessed at baseline and at follow-ups at 1-, 2- and 3-months following treatment initiation. Biomarkers will be measured at baseline and at 1- and 3-months follow-ups (Figs 1 and 3).

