### Sample size

The sample size has been previously calculated through the G-Power program, assuming an effect size of 0.35 for the primary outcome, a statistical power of 80% and an alpha error probability of 0.05. This showed that at least 22 participants per group are needed. Assuming a dropout rate of 10–15%, a total of 50 participants is intended. This analysis is based on a previous study on this topic [62].

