### Allocation and randomization

Individuals meeting the inclusion criteria will be randomly allocated to one of two treatment arms: (1) IVR plus exercise or (2) exercise alone.

Each patient will be assigned an alphanumeric code for identification, thus respecting their anonymity. To carry out the simple randomization procedure, the principal investigator will receive a list of the alphanumeric codes of the participants and will carry out a random assignment of the subjects in the 2 intervention groups using the SPSS statistical program. Allocation concealment will be ensured using opaque, sealed envelopes. A designated research assistant, independent of the assessment team, will open each envelope to assign participants to their respective intervention or control groups.

Participants will be randomized into intervention and control groups using a predefined randomization scheme, following the provision of informed consent and confirmation of clinical eligibility.

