### Statistics

Data analysis will be performed using SPSS version 30.0 (SPSS Inc., Chicago, IL, USA). Descriptive statistics will be used to summarize the demographic characteristics and baseline clinical, clinimetric and biomarker measurements of the sample. Continuous variables will be reported as mean ± standard deviation (SD), while categorical variables will be presented as frequencies (n) and percentages (%). For quantitative variables that do not follow a normal distribution, the median and interquartile range (IQR) will be used to describe the data.

For the primary analysis, a linear mixed-effects model will be used to compare changes in the dependent variables across the three time points between the two groups. The model will include fixed effects for site (Spain vs Chile) and baseline pain scores, along with group, time, and their interaction, as well as random intercepts for participants to account for within-subject correlations.

In addition to the primary analysis, bivariate correlation analyses (Pearson or Spearman, depending on the distribution of the variables) will be performed to examine the associations between the key variables at each time point.

To explore potential confounding variables, a series of covariate analyses will be performed, adjusting for baseline values of the dependent variables, age, gender, and other relevant demographic or clinical characteristics.

Statistical significance will be set at a p-value of <0.05 for all tests. Effect sizes (Cohen’s d) will be calculated for the main effects of the intervention to assess the magnitude of the group differences, and results will be presented with 95% confidence intervals.

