### Statistical population and handling of missing data

Primary analyses will follow the intention-to-treat principle, including all randomized participants as allocated, regardless of adherence or dropout. To handle missing outcome data, we will use linear mixed-effects models, which provide valid inference under the assumption that data are missing at random (MAR). However, we recognize that MAR may not always hold. If data exploration or external information suggests a missing not at random (MNAR) mechanism, we will conduct sensitivity analyses using pattern-mixture models or selection models to assess the robustness of our findings.

Biomarkers will be analyzed exclusively within the Spanish cohort, as these measures are not collected in Chile. All biomarker-related analyses will therefore be site-specific and reported separately. For these outcomes, linear mixed-effects models will be applied with time (baseline, 1-month, and 3-month) as a repeated factor and group (IVR + exercise vs exercise alone) as a fixed factor, including random intercepts for participants. Effect sizes and 95% confidence intervals will be presented. Missing biomarker data will be handled within the same mixed-model framework under MAR assumptions, with sensitivity analyses for MNAR scenarios as described above.

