### Adverse events and safety reporting

Participants will be actively monitored for any health-related issues throughout the course of the trial. All health events will be thoroughly documented, evaluated for intensity, and examined to determine any potential connection to the intervention. In the case of serious health events, these will be promptly reported to the appropriate ethics review boards and regulatory institutions in line with applicable policies. A complete account of both non-serious and serious health-related events will be included in final publications and official trial documentation.

In this regard, we will check some screening criteria prior to immersive virtual reality exposure: participants will be screened for conditions that may predispose them to adverse reactions during VR use, including history of epilepsy or photosensitive seizures, severe cibersickness when using the virtual reality hardware, or vestibular disorders. Also, anxiety disorders, claustrophobia, uncorrected visual impairments or balance instability will be considered.

Regarding thresholds for discontinuation, participants will be dropped out from the study if they experience cybersickness (measured by the Fast Motion Sickness Scale), dizziness, musculoskeletal injury, or a persistent increase in pain above 7/10 for more than 2 consecutive sessions, the subject will be excluded from the study. Algo, acute symptoms including moderate to severe nausea, dizziness, disorientation, headache or eye strain persisting beyond 15 minutes post-session, and emotional distress or panic symptoms during exposure are considered for stopping the intervention.

Similarly, and with respect to monitoring procedures, each participant will be supervised by a trained physiotherapist. Also, participants will complete a brief adverse event checklist with the previously mentioned items before and after each session. All adverse events will be documented and reported according to CONSORT guidelines for non-pharmacological interventions.

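### An exclusion criterion that runs into the study period could be applied to remove randomised participants for analgesic use, losing their later pain scores

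*Protocol article*

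**What the plan says.** Under Exclusion criteria, the protocol article lists "Use of analgesic or anti-inflammatory medications within 24 hours prior to participation in the study and at any time during the study". The same list contains a second item that also concerns conduct during the trial: "Physiotherapy treatments concomitant to the realization of the study".

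Allocation and randomization places randomisation "following the provision of informed consent and confirmation of clinical eligibility".

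Adverse events and safety reporting gives thresholds for leaving the trial. One is "a persistent increase in pain above 7/10 for more than 2 consecutive sessions, the subject will be excluded from the study". Analgesic use is not among them.

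The Discussion takes up medication separately. Medication and co-interventions are to be monitored and restricted, participants are advised to keep their usual medicines, and no new treatment may be started. It states no consequence for a breach.

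The primary outcome is change from baseline in pain on the 0–10 numeric scale. On timing, the Results section says: "Clinical and clinimetric outcomes will be assessed at baseline and at follow-ups at 1-, 2- and 3-months following treatment initiation". The primary analysis follows intention to treat, "including all randomized participants as allocated, regardless of adherence or dropout", using a mixed model that assumes data are missing at random. On its covariates, Statistics says: "The model will include fixed effects for site (Spain vs Chile) and baseline pain scores".

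**The concern.** An exclusion criterion normally decides who may be randomised. The 24-hour half of this one can do that. The other half describes behaviour over the following three months, so a breach is observed in someone who already has an allocation. If the item is then enforced as an exclusion, a randomised participant leaves the study.

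The reason for leaving would probably be linked to the outcome. People with chronic shoulder pain take analgesics largely because they hurt, and the primary outcome is how much they hurt. Neither participants nor therapists are blinded, so use could also differ between arms. At stake are later pain scores that could have been collected at visits already in the schedule.

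**Working it through.** **1. The plan's own figures.** The article gives no rate of analgesic use, so there is no figure on this exact point to reproduce. The relevant stated figure is the sample size: 22 per group, 44 in all, and "a total of 50 participants is intended" after 10–15% dropout. The 44 reproduces as the between-group test of a repeated-measures ANOVA, reading the effect size 0.35 as Cohen's f with 4 measurements and an assumed correlation of 0.5. The noncentrality is f²·N·m/(1+(m−1)ρ) = 0.1225 × 44 × 4 / 2.5 = 8.62, and N = 44 is the smallest even total reaching 80% power. The dropout allowance is 50 − 44 = 6 participants, or 6/50 = 12%.

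**2. When each half of the criterion can be checked.**
- Use in the 24 hours before participation: at the eligibility check, before randomisation.
- Actual use during the study: after randomisation, apart from a short and immaterial interval between consent and allocation.

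**3. What follows a breach.** Two readings are open.
- Removal: the item stands under Exclusion criteria, and the safety section uses exclusion from the study for people already taking part. For similar events, the Experimental group section speaks only of stopping the intervention.
- Restricted co-treatment: the concomitant physiotherapy item has the same form, the safety thresholds omit analgesics, and the Discussion speaks of monitoring and restriction.

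No sentence chooses between them, and none says that a participant who takes an analgesic stays in follow-up.

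**4. Loss per removal, if removal is applied.** There are 3 post-baseline pain scores per participant (months 1, 2 and 3), so 50 × 3 = 150 are planned.

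| Removed | Scores lost | Share of 150 |
|---|---|---|
| before month 1 | 3 | 2.0% |
| between months 1 and 2 | 2 | 1.3% |
| between months 2 and 3 | 1 | 0.7% |

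The month-3 score is lost every time. The number of removals is unknown. As an assumed range, not from the documents:
- 2 removals lose 2–6 scores (1.3%–4.0%)
- 5 removals lose 5–15 scores (3.3%–10.0%)
- 10 removals lose 10–30 scores (6.7%–20.0%)

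**5. What the analysis can recover.** The mixed model keeps scores recorded before removal. It cannot supply scores never taken. Statistics refers to three time points. If these are the follow-ups, with baseline pain as a covariate, someone removed before month 1 has no outcome row and adds nothing to the primary model.

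**6. Illustration on assumed inputs, none from the documents.** The simulation used pain SD 2, within-person correlation 0.5, a true difference of −1.0, 100 per arm and 100 simulated trials. The model had random intercepts, baseline pain, group, time and their interaction. The probability of removal rose with pain.

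| Removal driven by | Retained, control v IVR | Month-3 estimate (simulation SE) |
|---|---|---|
| no removal | all | −1.01 (0.03) |
| previous recorded pain | 65% v 71% | −0.98 (0.03) |
| current unrecorded pain | 72% v 81% | −0.91 (0.03) |

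The model copes when recorded pain drives removal: the shift of 0.03 is within simulation error. When unrecorded pain drives it, the estimate shrinks by about 0.10, or 10%, with 19%–28% removed. This shows a possible mechanism and does not forecast this trial.

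**The case against.** The strongest reply is that the article never says follow-up ends. A reader might infer that the criterion orders withdrawal for any analgesic use. The documents do not support that: the safety section lists its thresholds without naming analgesics, and the Discussion describes monitoring and restriction. Taking a restricted drug can also be seen as non-adherence, which the intention-to-treat statement covers. All this stands, and it is why the point is conditional.

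A reader might also infer that the during-study half can do nothing before randomisation. That is too strong. Screening could ask whether a candidate expects to need analgesics, and the Discussion mentions selecting participants with compliance in mind. Only actual use has to wait until after allocation.

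A third inference is that the Discussion contradicts the exclusion list by allowing usual medicines. Daily analgesic users fail the 24-hour check, and usual medicines may mean other drugs. Conflicting instructions are possible only for intermittent users who pass that check.

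On size, 2 or 5 removals (4% or 10% of 50) would fit within the 12% dropout allowance if there were little other dropout. The simulated shrinkage was modest, and most of its removal rates exceeded the largest assumed above (10 of 50, 20%). Known removals for analgesic use could also count as grounds for the planned analyses under missing-not-at-random assumptions. These are fair limits on how much harm to expect. But a dropout allowance protects numbers, not comparability, and sensitivity models vary assumptions about values that could have been measured.

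Finally, a condensed article may leave the handling of restricted medication to the full protocol. That would answer a complaint about missing detail. Here the article states a rule, and the rule as placed permits removal.

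**Conclusion.** The point holds as a conditional weakness in a stated rule. Analgesic or anti-inflammatory use during the study is listed as an exclusion, although actual use can be observed only after randomisation. If it is enforced as listed, randomised participants could be removed for an event probably related to the primary outcome. Each removal would lose the month-3 score and up to two others, and the planned model could not supply them.

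This rests on two assumptions: that a site applies the item as an exclusion, and that analgesic use tracks pain. A reader might go further and conclude that the primary result will be biased. The documents do not support that, because they give no rate of use, no split by arm and no order to withdraw. Neither the size nor the direction of bias can be derived. The change is a cheap improvement that should be made.

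**What to change.** - In Exclusion criteria, limit the item to use in the 24 hours before participation, checked before randomisation.
- State that analgesic or anti-inflammatory use during the study is a restricted co-treatment. It is recorded under the monitoring the Discussion already plans, and it neither ends follow-up nor removes the participant from the analysis.
- In the Discussion, say whether the usual medicines that participants may keep include analgesics and anti-inflammatories.

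The cost is a wording amendment, with the additional ethics review that the article requires for protocol changes, and one medication question at visits already scheduled. The downside is that pain scores taken after analgesic use will reflect programme plus analgesic. The record of use lets a sensitivity analysis examine this; the Discussion already plans such analyses.
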